### **Considerations regarding NCFBE**

The incidence of NCFBE is increasing worldwide. Previously classified as a rare or orphan disease, the diagnosis has increased by 40% in the past several years (Flume, Chalmers et al. 2018) and the number of adults with bronchiectasis in the United States is estimated at 350,000 - 500,000 (Weycker, Hansen et al. 2017); i.e., much higher than the number of adults with CF (which amount to 30,000-40,000). Unfortunately, there are no curative therapies or medications specifically approved to address fundamental mechanisms that underlie NCFBE.

Trikafta™ is approved for patients with CF carrying at least one copy of the common F508del variant or a number of other CFTR abnormalities. Trikafta™ is a combination of three CF drugs, elexacaftor, ivacaftor, and tezacaftor (ETI), that helps CFTR proteins work more effectively. Patients with common forms of CF typically exhibit a robust pulmonary benefit from Trikafta™ within several days of initiating treatment (Middleton, Mall et al. 2019, Barry, Mall et al. 2021).

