## Protocol Title: Evaluating Trikafta for the treatment of patients with non-cystic fibrosis bronchiectasis (NCFBE)

Trikafta™ is not prescribed or approved for NCFBE and has not been considered of benefit for patients with NCFBE. We hypothesize that a drug such as Trikafta™, that markedly activates both wild type and mutant CFTR *in vivo*, will enhance mucociliary clearance and should improve respiratory function (FEV1) in a subset of patients with NCFBE. Even if one in ten patients with NCFBE shows significant improvement in FEV1 following Trikafta™, this would constitute a major discovery and provide new hope for tens of thousands of individuals in the US with an otherwise untreatable and lethal lung disease.

Figure 1. Summary of trial design.

[figure not shown]

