The 'wash-out' visit will be conducted on day 56 (+/-2) which will require approximately 4-6 hours to complete concomitant medication review, interval medical history, adverse event assessment, physical exam, safety laboratory assessments (CBC/Diff, RENAL/LFT chemistry panel, and urinalysis), questionnaire, sweat chloride, urine pregnancy test for females, cutaneous punch biopsy (3mm) if necessary to obtain additional cells, O2 saturation, and spirometry. The cutaneous punch biopsy may occur within  $\pm$  14 days of the day 56 visit based on dermatology clinic schedule availability. No further data will be collected after all study procedures and measurements are completed.

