Secondarily, we will serially evaluate clinical outcomes of interest prior to and after the start of therapy. Change in clinical measurements (in addition to spirometry – sweat chloride, weight/BMI, quality of life) will be monitored. A complementary analysis evaluating the percentage of participants with  $\geq 15$  mmol/L decline in sweat chloride will also be reported. With a previously estimated 9.7 mmol/L standard deviation of the change in sweat chloride for successful modulator trials (Boyle et al., 2014; Vermeulen et al., 2017), an anticipated 6% of responders would be expected by chance alone. Therefore, the treatment response prevalence will be compared to a reference rate of 6%. For longitudinal FEV1 through day 28 and for secondary endpoints (absolute change in sweat chloride, QOL questionnaire, and weight/BMI from baseline through day 28), means at each time point and changes over time will be summarized along with corresponding confidence intervals estimated by mixed effects models to account for within-subject correlation.

Changes in FEV1 following treatment with Trikafta™ will be correlated with secondary clinical outcome measures. A non-linear Spearman's correlation coefficient will be estimated for each measure paired with iPS cell responses *in vitro*, with corresponding fitted curves displayed graphically along with coordinates for participant's paired *in vivo* and *in vitro* responses.

For other outcomes of interest including sweat chloride levels, quality of life, and weight/BMI, we will also apply a mixed effect model to examine the change in these measures over the study duration. Models will include a subject-specific intercept, to account for variability among subjects prior to the start of the treatment, and a categorical variable for time (baseline, day 14, day 28, day 56). A Dunnett's post-hoc comparisons procedure will be used to determine which time points demonstrated a significant change from baseline. Using the same mixed effects models, we will include  $\Delta$  Isc as predictors of *in vivo* improvement. We will also test the interaction between time and  $\Delta$  Isc to determine when *in vitro* response is most associated with change in clinical response. Adverse events and other safety endpoints will be tabulated and reported using counts and percentages or means and standard deviations, as appropriate.

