| LB = Lower Bound, UB = Upper Bound
Note: Thirty total patients will be enrolled in the unlikely event that a subject discontinues participation (e.g., due to elevated liver function tests, skin rash, or for other reasons). |                                   |                                                                                      |                                       |

With a sample size of 16 (29) participants, we anticipate a 97% (>99%) power to detect a mean sweat chloride decrease of 10 mmol/L assuming a standard deviation of 9.7 mmol/L (Boyle, Bell et al. 2014, Vermeulen, Le Camus et al. 2017) under a two-sided 0.05 alpha-level paired t-test. With a higher standard deviation of 15 mmol/L, the power decreases to 70.3% (93.4%) to detect a mean decrease of 10, but we retain 96.2% (>99%) power to detect the hypothesized mean decrease of 15 mmol/L with a sample size of 16 (29) patients.

SAEs and AEs will be tabulated using standard coding terms sorted by System Organ Class (SOC). The incidence of AEs will be tabulated by seriousness and severity. The number of SAEs and AEs will be summarized as follows: (i) The proportion of subjects with at least one (S)AE, (ii) The average number of (S)AEs per subject, and (iii) The rate of (S)AEs per subject week of follow-up.

**Expected Outcomes** Subjects will be recruited by study investigators as above. Please note that based on considerable past experience conducting clinical trials and past collaborations with NCFBE clinical leadership throughout the US, we do not have concerns regarding our ability to perform the patient-oriented study described here, or to propagate and characterize iPS cells (Crane, Kramer et al. 2015, Mou, Brazauskas et al. 2015, Hawkins, Kramer et al. 2017, Jacob, Morley et al. 2017). The ‘main’ study protocol will evaluate the clinical benefit of Trikafta™ in patients with NCFBE. In addition, the study will furnish one test of our hypothesis that thresholds of CFTR activity in differentiated iPS cells *in vitro* predict benefit following Trikafta™ *in vivo*. If a strong correlation can be established between Trikafta™ response *in vitro* and *in vivo* (e.g., FEV1), the clinical results will provide evidence regarding usefulness of *in vitro* models for predicting clinical efficacy in this setting.

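### The secondary mixed models name only a subject-specific intercept; if response differs between subjects, their standard errors for change from baseline are wrong

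*Protocol*

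**What the plan says.** Section 7 of the protocol describes mixed models in two places.

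- The first covers longitudinal FEV1 and the secondary endpoints through Day 28. Means and changes, with confidence intervals, are to be "estimated by mixed effects models to account for within-subject correlation". No random-effects or residual structure is named.
- The second covers sweat chloride, quality of life and weight/BMI over the whole study. Here the structure is given: "Models will include a subject-specific intercept, to account for variability among subjects prior to the start of the treatment", together with "a categorical variable for time (baseline, day 14, day 28, day 56"). Inference follows: "A Dunnett's post-hoc comparisons procedure will be used to determine which time points demonstrated a significant change from baseline". The same models are then reused with delta Isc as a predictor and with a time by delta Isc interaction.

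Three other statements bear on the variance of change.

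- Section 3 hypothesises improvement "in a subset of patients with NCFBE".
- Section 3 also says that patients with common forms of CF usually benefit "within several days of initiating treatment".
- Section 6 makes the last visit an off-drug wash-out: this "visit will be conducted on day 56 (+/-2"), four weeks after the 28-day drug supply ends.

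**The concern.** The intercept is justified by differences between subjects before treatment. Nothing in the described model represents differences between subjects in how much they respond, which is what the trial sets out to study.

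A random intercept with independent, equal-variance residuals cancels out of every within-subject change. All such changes then share one variance. If some subjects respond and others do not, a change from off drug to on drug carries extra variance that a change between two off-drug visits, or between two on-drug visits, does not. The model pools these into one average.

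At stake are the standard errors behind the secondary visit-by-visit comparisons, and those behind the interaction test of whether in vitro response tracks clinical change over time. Under the protocol's own expectations, the error overstates certainty on drug and blurs the wash-out comparison.

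**Working it through.** **Inputs.** From section 7: four visits (baseline, Days 14, 28 and 56), n = 16 at stage 1 and 29 in total, and SDs of sweat chloride change of 9.7 and 15 mmol/L. The protocol offers the second as an alternative ("With a higher standard deviation of 15 mmol/L"). Reading 9.7 as noise and 15 as total is an assumption made here.

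**Step 1: the plan's own figures.** No figure is given for the mixed models. The nearest are the paired t-test powers for sweat chloride, and they reproduce with the noncentral t distribution:

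| Mean decrease, SD | n=16: stated / recomputed | n=29: stated / recomputed |
|---|---|---|
| 10, 9.7 | 97% / 97.05% | >99% / 99.97% |
| 10, 15 | 70.3% / 70.31% | 93.4% / 93.38% |
| 15, 15 | 96.2% / 96.19% | >99% / 99.94% |

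**Step 2: true variance of change.** Let s² be the residual variance at one visit and τ² the between-subject variance of response. Take full response at Days 14 and 28 and full wash-out at Day 56.

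- Baseline to Day 14, baseline to Day 28, Day 14 to Day 56, Day 28 to Day 56: 2s² + τ²
- Baseline to Day 56, Day 14 to Day 28: 2s²

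**Step 3: variance the model uses.** With complete data, the random-intercept model assigns every change the mean of the six variances: 2s² + (4/6)τ² = 2s² + (2/3)τ². For any τ² > 0 this is below the truth at Days 14 and 28 and above it at Day 56.

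**Step 4: numbers.**

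- 2s² = 9.7² = 94.09
- τ² = 15² − 9.7² = 225 − 94.09 = 130.91, so τ = 11.4
- Model variance = 94.09 + (2/3)(130.91) = 181.36, so the model SD of change is 13.47
- SE ratio (model/true) at Days 14 and 28: 13.47/15 = 0.898
- SE ratio at Day 56: 13.47/9.7 = 1.388

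**Step 5: simulation of this scenario, n=29** (results move by a few tenths of a percentage point between runs).

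| Quantity | With response heterogeneity | Without |
|---|---|---|
| Unadjusted 95% coverage, Days 14 and 28 | about 92% | about 95% |
| Unadjusted 95% coverage, Day 56 | about 99% | about 95% |
| Dunnett familywise error | about 6% | about 5% |
| Type I error, time by delta Isc (delta Isc unrelated to response) | about 7% | about 5% |

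At n=16 coverage is much the same (92.1% and 99.2%). With visit-specific variances it returns to about 95% at every visit. The mean half-width at Day 28 then goes from 4.95 to 5.65, and at Day 56 from 4.95 to 3.66. A mixture in which 15% of subjects fall by 30 mmol/L gives 92.0% at Day 28 and 99.0% at Day 56, so normality of response does not drive the result.

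**Step 6: range over the assumed on-drug SD of change** (noise SD held at 9.7, same pattern).

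| On-drug SD | SE ratio, Days 14/28 | SE ratio, Day 56 | Coverage, Days 14/28 | Coverage, Day 56 |
|---|---|---|---|---|
| 12 | 0.940 | 1.163 | 93.5% | 97.7% |
| 15 | 0.898 | 1.388 | 92.1% | 99.2% |
| 20 | 0.863 | 1.780 | 90.6% | 99.9% |

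Under full response and full wash-out the on-drug ratio cannot fall below √(2/3) = 0.816.

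**Step 7: other response patterns** (9.7 and 15 as before).

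- Full response by Day 14 and full persistence at Day 56: three of the six changes carry τ², so the model variance is 94.09 + 130.91/2 = 159.5, SD 12.63 and ratio 0.842 at all three visits. Coverage is about 90% throughout and Dunnett familywise error about 9–10%.
- Half the response at Day 14 and full persistence: coverage is about 96.9% at Day 14 and 89.4% at Day 56, the reverse of Step 5 at both visits.
- Crossover points: with full wash-out, Day 14 is too narrow only if its response exceeds about 72% of the Day 28 response. With full response by Day 14, Day 56 is too wide only if less than about 67% of the response persists.

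**The case against.** **The text says that the models include an intercept, not that they contain nothing else.** SAS can combine a random intercept with visit-specific residual variances, and a separate SAP may do so. This stands as a limit: the error follows from independent, equal-variance residuals. But that is the default reading, section 7 is itself headed as the statistical analysis plan, and the stated purpose of the intercept covers pre-treatment variability only. The point therefore concerns a stated method, not only an omitted detail.

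**A reader might infer that the FEV1 results or the main test of in vitro prediction are compromised.** The protocol does not support that. The FEV1 response rate has an exact Blaker interval and continuous FEV1 a paired t-test. In vitro prediction rests mainly on Spearman correlation and ANCOVA of delta Isc. None of these uses the mixed model. The intercept sentence does not cover longitudinal FEV1, whose covariance is unstated. Sweat chloride at Day 28 is also powered as a paired t-test, and a sensitivity analysis is to replicate the FEV1 analysis with it, so a correctly sized Day 28 contrast is already contemplated.

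**A reader might also infer that on-drug intervals are always too narrow and Day 56 always too wide.** Step 7 shows otherwise. Weight/BMI may well persist after wash-out.

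**The planned procedure is Dunnett, not unadjusted intervals.** In the main scenario the familywise error is only about 6%, because the conservative Day 56 comparison offsets the liberal on-drug ones. That is correct, and the effect there is mild.

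**The SDs are alternatives in the protocol.** The protocol does use 9.7 for the response rate expected by chance, which supports reading it as noise. Splitting 15 into noise and response remains an assumption.

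**Conclusion.** The point holds for the secondary mixed models of sweat chloride, quality of life and weight/BMI, and for their reuse with delta Isc. Under the default residual structure, response that varies between subjects makes their standard errors wrong, and the trial's own hypothesis predicts such variation. Which intervals are too narrow depends on the speed of onset and the extent of wash-out.

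The size is modest. In the illustrative scenario the on-drug standard errors are about 10% too small and the Day 56 standard error about 39% too large. The interaction figure of about 7% assumes that delta Isc is unrelated to response; if it does predict response, part of the heterogeneity is absorbed. If response does not vary between subjects, the model is correct. This is worth correcting before analysis, but it does not threaten the primary conclusions.

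**What to change.** In the section 7 paragraph on the other outcomes, replace the intercept-only description with an unstructured within-subject covariance over the four visits (4 variances + 6 covariances = 10 parameters) and Kenward-Roger degrees of freedom. State the fallback in advance: heterogeneous Toeplitz if the unstructured model does not converge, then paired per-visit contrasts. Apply this to the sweat chloride, quality of life and weight/BMI models and to the delta Isc and time by delta Isc models. For consistency, state the same structure for the longitudinal FEV1 model.

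The cost is about a sentence and a change to the SAS model statement, with no new data and no change in sample size. On-drug intervals become slightly wider, and with 29 subjects the fallback may be needed.

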**Protocol Title: Evaluating Trikafta for the treatment of patients with non-cystic fibrosis bronchiectasis (NCFBE)**

subject research, we will evaluate therapeutic response in individual subjects by an interrupted time series (ITS) method. Briefly, in the absence of an independent control group, ITS analysis is a quasi-experimental design in which each subject acts as their own control and is followed serially in time prior to and after an interruption (in this case, the start of treatment). If the treatment has causal impact, the post-intervention time series will have a different level or slope than the pre-intervention series. Time series models also have the power to test and correct for possible cyclical patterns and outliers. Using segmented regression analysis, we will conduct ITS models for each of the subjects enrolled in the trial. A significant change in slope from the pre-treatment period will indicate a significant treatment effect. ITS models will be constructed for each outcome of interest where historical and pre-treatment data are available. The change in slope will also be correlated with the *in-vitro* response using Spearman's rank-order correlation coefficient.

All analyses will be conducted using the intention to treat principal, where all subjects will be included in analysis regardless of how long they took the study medication. Statistical significance will be assessed at the 0.05 level and analyses conducted using SAS v. 9.4 (SAS Institute; Cary, NC).

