**Protocol Title: Evaluating Trikafta for the treatment of patients with non-cystic fibrosis bronchiectasis (NCFBE)**

---

Spirometry may be performed either pre- or post-bronchodilator at Screening. At all other visits, spirometry should be performed pre-bronchodilator. However, if patient is unable to withhold bronchodilator use at the Day 1 visit, then the spirometry assessment will be considered 'post-bronchodilator' and attempts should be made to collect spirometry post-bronchodilator at remaining visits.

In order for a spirometry assessment to be considered pre-bronchodilator, subjects should adhere to the following:

- Subjects should refrain from using short-acting bronchodilators (e.g., albuterol) or anticholinergic (e.g., ipratropium bromide [Atrovent®]) for more than 4 hours before the spirometry assessment.
- Subjects should refrain from using long-acting bronchodilator (e.g., salmeterol) for more than 12 hours before the spirometry assessment; and
- Subjects should refrain from using once-daily, long-acting bronchodilator (e.g., tiotropium bromide [Spiriva®]) for more than 24 hours before the spirometry assessment.

Sources of Patient-Derived Material:

- Review of patient medical records and demographic information
- History and physical exam
- Blood and urine for safety studies (<6 tablespoons of blood per visit)
- Sweat chloride results
- Questionnaire data
- Spirometry (FEV1, FVC, and FEF25-75%) calculated per Hankinson equation
- Cutaneous punch biopsy (3 mm)/iPS cell derivation
- O2 saturation
- EKG
- CFTR genotype
- Pregnancy test
- Drug accountability
- Adverse event assessment
- Concomitant medication review

Note: Data collection forms for the study are in preparation.

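### The single-subject ITS rule judges effect by slope change alone, which a gain complete by Day 14 and held to Day 28 need not produce; the rule should use a level contrast

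*Protocol*

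**What the plan says.** Section 7 of the Protocol adds a modified N-of-1 analysis to the aggregate one, for the stated purpose of comparison with the iPS results. It specifies: "Using segmented regression analysis, we will conduct ITS models for each of the subjects enrolled in the trial". It describes what an effect would look like: "If the treatment has causal impact, the post-intervention time series will have a different level or slope than the pre-intervention series". It then gives one decision rule, "A significant change in slope from the pre-treatment period will indicate a significant treatment effect", and carries one quantity forward: "The change in slope will also be correlated with the *in-vitro* response using Spearman's rank-order correlation coefficient". No model equation, no minimum number of historical values and no rule for Day 56 is given.

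Three other places bear on this.
- **Onset.** Section 3 (Considerations regarding NCFBE) says: "Patients with common forms of CF typically exhibit a robust pulmonary benefit from Trikafta™ within several days of initiating treatment".
- **Schedule.** In Section 6, Day 7 is a phone call, so on-drug spirometry is at Days 14 and 28 only. Day 56 is a wash-out visit. Section 16 anticipates that respiratory function returns to baseline once the drug is stopped.
- **Bronchodilator status.** Section 6 says: "Spirometry may be performed either pre- or post-bronchodilator at Screening". Later visits should be pre-bronchodilator, with an exception for subjects who cannot withhold the bronchodilator at Day 1.

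**The concern.** The paragraph recognises two signatures of an effect, level and slope, and then drops the level without giving a reason. A gain that is complete before the first on-drug measurement is a change of level. It leaves no trace in the slope between Days 14 and 28.

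At stake is the individual-level comparison with the iPS assay. If the slope change is unrelated to a subject's true gain, its correlation with the in-vitro response carries little information. If the slope change runs opposite to the gain, the correlation could take the wrong sign. Such a result could be read as evidence against the assay and would sit awkwardly beside the main FEV1 correlation.

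**Working it through.** The protocol states no power or error rate for the ITS analysis, so there is no figure to reproduce.

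**Inputs from the protocol.** Spirometry at Screening, Day 1, Day 14, Day 28 and Day 56; treatment for 28 days; two-sided alpha 0.05; responder threshold above 5 points of % predicted FEV1.

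**Assumptions (the protocol gives no figures).** Within-subject visit SD 3 or 5 points; gain J = 5 or 10 points, complete before Day 14, held to Day 28 and gone by Day 56; 4, 8 or 20 historical values 90 days apart; independent normal errors.

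**Model.** y = b0 + b1·t + b2·post + b3·(t − start)·post, fitted per subject. The rule tests b3.

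**1. Post-start points at Days 14 and 28.** The post-start slope is (J − J)/14 = 0 for any J, and the pre-treatment slope is 0, so b3 = 0. The rejection rate is therefore alpha. Simulation gave a significant positive slope in 2.4–2.6% of runs. The post-start slope alone has SE = SD·√2/14, which is 3 × 1.414/14 = 0.30 points per day at SD 3.

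**2. Day 56 added to the post-start segment.** The values are J, J, 0 at days 14, 28, 56. Mean day = 98/3 = 32.67, with deviations −18.67, −4.67 and +23.33. Sum of squares = 348.4 + 21.8 + 544.4 = 914.7. Cross-product = J × (−18.67 − 4.67) = −23.33J. Slope = −23.33J/914.7 = −0.0255J per day, or −0.357J per 14 days: −1.8 for J = 5 and −3.6 for J = 10.

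Simulated share of subjects with a significantly **negative** slope change:

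| Gain, SD | 4 historical | 8 historical | 20 historical |
|---|---|---|---|
| 10 points, SD 3 | 49% | 59% | 67% |
| 10 points, SD 5 | 23% | 27% | 31% |
| 5 points, SD 3 | 17% | 21% | 23% |

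A significant positive slope occurred in at most 0.1% of these runs.

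**3. Hinge model (b2 removed), Days 14 and 28 only.** The jump is forced into the slope. Power at SD 3 with 4 to 20 historical values is 54–94% for 10 points and 21–43% for 5 points; for 10 points at SD 5 it is 28–57%. With Day 56 included, power falls to 0.1–8%.

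**4. Level contrast with a pooled SD treated as known.** Power = Φ(J/SE − 1.96).
- All five visits, Day 56 counted as off-drug: SE = SD·√(1/2 + 1/3), which is 2.74 at SD 3 and 4.56 at SD 5.
- Days 14 and 28 against Screening and Day 1: SE = SD·√(1/2 + 1/2), which is 3 or 5.

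| Gain, SD | Five visits | Without Day 56 |
|---|---|---|
| 10 points, SD 3 | 95% | 91% |
| 10 points, SD 5 | 59% | 52% |
| 5 points, SD 3 | 45% | 38% |
| 5 points, SD 5 | 19% | 17% |

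**The case against.** Several objections have force.

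- **The model is not fixed.** A hinge model without Day 56 can pick up a jump as slope, as step 3 shows. This stands as a limit. The protocol does not specify that model, and its own reference to level makes a level term the more natural reading.
- **Day 56 may not belong to the post-start segment.** Section 7 runs longitudinal FEV1 through Day 28 and includes Day 56 in the mixed models for other outcomes. Against that, the ITS paragraph names a single interruption, the start of treatment. The matter is open, so the negative-slope figures are conditional.
- **The onset is stated for CF.** No time course is given for NCFBE. A gain still growing between Days 14 and 28 would produce some positive slope. This stands, although it is the only onset information the protocol offers.
- **The power comparison is not like for like.** The contrast treats a pooled SD as known, while the slope rule is a per-subject t-test on few degrees of freedom. This stands, and it is why the contrast is shown over a range.

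A reader might also infer three stronger points that the documents do not support. First, that no test exists because Screening, Day 1, Day 14 and Day 28 give four observations for four parameters: that arises only without historical data, and the protocol limits ITS to outcomes for which historical data are available. Second, that the bronchodilator rule creates a false pre-treatment decline: this needs a post-bronchodilator Screening followed by a pre-bronchodilator Day 1, which is permitted but not prescribed. Third, that validation of the iPS assay fails: Section 7 separately compares ΔIsc by responder status and correlates it with change in FEV1, and neither uses the ITS.

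**Conclusion.** The stated rule is mismatched to the effect the protocol leads one to expect. In a level-plus-slope model with an early, sustained gain, it detects responders no more often than non-responders: 5% two-sided, 2.5% in the right direction. That result is algebraic and does not depend on the SD. The negative-slope rates depend on Day 56 being in the post-start segment, on wash-out being complete and on the assumed SDs. Weakening or inversion of the in-vitro correlation follows in direction from these results but was not simulated.

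The damage is confined to the supplementary N-of-1/ITS analysis and its correlation with the in-vitro response. The primary response-rate test and the main Spearman correlation are untouched. It would be going too far to say the rule must miss or invert every true response, because that depends on a model form, a time course and a Day 56 placement that the protocol does not fix. This is a minor to moderate point, worth correcting, held with medium confidence.

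**What to change.** Define the individual effect as a level contrast: the mean of Days 14 and 28 minus the mean of the pre-treatment values. Test it against a within-subject SD pooled over subjects, and correlate this contrast with ΔIsc. Treat Day 56 as a separate off-drug phase, and use it as an off-drug value only if complete wash-out is assumed and that assumption is stated. Use Screening FEV1 in the contrast only when its bronchodilator status matches Day 1. Keep the slope change as exploratory, with the model equation written out.

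The cost is analysis wording; no visits or subjects are added. The contrast assumes a common within-subject SD, and leaving out unmatched Screening values loses some precision. Single-subject power stays modest: with all five visits, 95% for 10 points at SD 3, but 45% for 5 points at SD 3 and 19% for 5 points at SD 5. The gain is that the contrast measures the intended quantity with the right sign.
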